### Blood sampling and time points for ctDNA detection

Peripheral venous blood samples (10 milliliters [mL] per time point) will be collected into ethylenediaminetetraacetic acid (EDTA)-anticoagulated tubes (Becton Dickinson, Franklin Lakes, New Jersey, USA) at the following predefined time points to capture ctDNA dynamics throughout the treatment course and follow-up period:

T0 (baseline): Within 7 days before initiation of CCRT. This baseline sample will establish the pretreatment HPV ctDNA level as a reference point and will be correlated with baseline tumor burden assessed by imaging and clinical examination.

T1 (mid-treatment): After 3–4 weeks of CCRT (approximately 15–20 fractions of radiotherapy and 3–4 cycles of concurrent chemotherapy).

T2 (end of CCRT): Within 1 week after completion of all CCRT including brachytherapy.

T3 (first evaluation): At 3 months (± 2 weeks) after completion of CCRT, coinciding with the first scheduled imaging assessment.

Follow-up sampling: Every 6 months (± 4 weeks) thereafter for up to 24 months from the completion of CCRT, or until disease progression, death, withdrawal of consent, or study completion, whichever occurs first. Additional blood samples may be collected at unscheduled visits if disease recurrence or progression is clinically suspected, to correlate ctDNA status with disease status.

Blood samples will be processed according to a standardized protocol to ensure consistency and minimize preanalytical variability. Specifically, blood samples must be maintained at room temperature and processed within 2 hours of collection to prevent cell lysis and release of genomic DNA that could dilute ctDNA signals. Samples will be centrifuged at 1,600 × g for 10 minutes at 4 °C to separate plasma from cellular components. The plasma supernatant will be carefully transferred to a new tube without disturbing the buffy coat layer and will be subjected to a second centrifugation at 16,000 × g for 10 minutes at 4 °C to remove any residual cells and debris. The resulting cell-free plasma will be aliquoted into 1-mL cryovials, labeled with unique identifiers, and stored immediately at –80 °C until batch analysis. All samples will be tracked using a laboratory information management system to ensure chain of custody and prevent sample mix-ups.

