
### Clinical evaluation and imaging

Treatment response will be assessed at 3 months (± 2 weeks) after completion of CCRT using pelvic MRI as the primary imaging modality, supplemented by PET-CT in selected cases based on clinical indication (such as suspected distant metastases or equivocal MRI findings). MRI will be performed using a 1.5-Tesla or 3-Tesla scanner with appropriate pelvic coils, and will include multiparametric sequences such as T2-weighted imaging in axial, sagittal, and coronal planes, T1-weighted imaging, diffusion-weighted imaging (DWI) with apparent diffusion coefficient (ADC) mapping, and dynamic contrast-enhanced (DCE) imaging. Tumor response will be evaluated according to Response Evaluation Criteria in Solid Tumors (RECIST) version 1.1, with complete response (CR) defined as disappearance of all target lesions, partial response (PR) as at least a 30% decrease in the sum of diameters of target lesions, progressive disease (PD) as at least a 20% increase in the sum of diameters of target lesions or appearance of new lesions, and stable disease (SD) as neither sufficient shrinkage to qualify for PR nor sufficient increase to qualify for PD.

Follow-up imaging will be performed every 6 months (± 4 weeks) for the first 2 years, then annually for years 3–5, or more frequently if clinically indicated based on symptoms suggestive of disease recurrence (such as abnormal vaginal bleeding, pelvic pain, or new onset of symptoms). Additional imaging studies such as chest CT, abdominal CT, or bone scintigraphy may be performed at the discretion of the treating physician if metastatic disease is suspected. All imaging studies will be reviewed by radiologists with expertise in gynecologic oncology who are blinded to ctDNA results, and findings will be documented using standardized radiology report templates. Imaging-detected disease recurrence will be confirmed by biopsy whenever feasible and clinically appropriate to obtain histopathologic confirmation.

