Secondary outcome include: (1) Overall survival (OS), defined as the time from the initiation of CCRT to death from any cause, with patients who are alive at the time of analysis censored at the date they were last known to be alive; (2) Objective response rate (ORR), defined as the proportion of patients achieving CR or PR at the first imaging assessment (3 months post-CCRT) according to RECIST version 1.1 criteria; (3) Dynamic changes in plasma HPV ctDNA levels expressed as continuous variables (copies per mL) and categorical variables (detectable versus undetectable) at predefined time points (T0, T1, T2, T3, and follow-up time points) during and after CCRT, including assessment of ctDNA clearance kinetics (time to first undetectable ctDNA), nadir ctDNA levels, and patterns of ctDNA dynamics (rapid clearance, slow clearance, persistent detection, or reappearance after initial clearance); (4) Predictive performance of HPV ctDNA for disease recurrence, including calculation of sensitivity (proportion of patients with recurrence who have detectable ctDNA), specificity (proportion of patients without recurrence who have undetectable ctDNA), positive predictive value (PPV; probability of recurrence given detectable ctDNA), negative predictive value (NPV; probability of no recurrence given undetectable ctDNA), and area under the receiver operating characteristic curve (AUC-ROC) for ctDNA as a predictive biomarker, with 95% confidence intervals (CIs); and (5) Concordance between HPV ctDNA status and imaging-based assessment (MRI and/or PET-CT) in detecting residual disease at 3 months post-CCRT and early relapse during follow-up, assessed using Cohen’s kappa statistic and contingency table analysis. Additionally, we will explore the lead time advantage of ctDNA detection, defined as the time interval between ctDNA-detected recurrence and imaging-detected recurrence in patients who experience disease progression (20). The detailed schedule of assessments follows the SPIRIT framework and is presented in **Table 1**, which outlines all study procedures, evaluations, and time points from screening through close-out.

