### Sample size calculation

The sample size was calculated based on the primary endpoint of 2-year progression-free survival (PFS), comparing patients with detectable versus undetectable plasma HPV ctDNA at 3 months after completion of CCRT (T3). Institutional historical data indicate a 2-year PFS of approximately 75% in the ctDNA-negative group, while published studies suggest a rate of approximately 50% in the ctDNA-positive group (21). Based on prior studies of HPV-associated malignancies, we conservatively estimated that 30% of patients would be ctDNA-positive at the T3 assessment. Sample size was estimated using the log-rank test for comparing survival curves between two groups: 
$\text{n}={\left({\text{Z}}_{1}-\alpha {/}_{2}+{\text{Z}}_{1}-\beta \right)}^{2}/\left[{\left(\ln\text{HR}\right)}^{2}\times \text{p}\left(1-\text{P}\right)\right]$.

where 
$Z_{1-\alpha /2}=1.96$ for a two-sided α = 0.05, 
$Z_{1-\beta }=0.842$ for 80% power, and *p* = 0.30 represents the proportion of patients expected to be ctDNA-positive. The hazard ratio (HR) was derived from the assumed survival probabilities (
$S_{\text{ctDNA}+}=0.50$, 
$S_{\text{ctDNA}-}=0.75$), yielding an estimated HR of 2.41. Using these assumptions, a minimum of 48 evaluable patients is required to achieve 80% power to detect a difference in 2-year PFS at a two-sided significance level of 0.05. Allowing for an anticipated 15% attrition rate, the total target enrollment is 57 patients. This sample size is considered feasible for recruitment at a single high-volume tertiary cancer center over the planned 2-year enrollment period and is supported by effect sizes reported in prior studies of ctDNA as a prognostic biomarker in HPV-associated cancers (21, 22).

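### The exploratory ctDNA lead time is one-sided by design, so on its own it cannot show that ctDNA detects recurrence before imaging

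*Protocol article*

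**What the plan says.** The analysis is introduced under Outcome measures, after the five numbered secondary outcomes: "Additionally, we will explore the lead time advantage of ctDNA detection". The interval is "defined as the time interval between ctDNA-detected recurrence and imaging-detected recurrence in patients who experience disease progression". The article gives no rule for a progressor in whom ctDNA was never detected.

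Under Blood sampling and time points for ctDNA detection, the T3 sample is taken "At 3 months (± 2 weeks) after completion of CCRT, coinciding with the first scheduled imaging assessment". Later samples are six-monthly (± 4 weeks) up to 24 months, "or until disease progression, death, withdrawal of consent, or study completion, whichever occurs first". There is one optional addition: "Additional blood samples may be collected at unscheduled visits if disease recurrence or progression is clinically suspected". No sample is scheduled after progression.

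Under Clinical evaluation and imaging, scans follow the same rhythm: "Follow-up imaging will be performed every 6 months (± 4 weeks) for the first 2 years", or sooner for symptoms. Table 1 puts ctDNA, MRI and the RECIST assessment in the same columns from 3 months onward.

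**The concern.** A lead time needs two dates. A progressor with no ctDNA detection has only one and so contributes no value. Those patients are the test's misses, and they may not be rare: the Feasibility and limitation section expects about 30-40% of patients to be ctDNA-negative at baseline despite HPV-positive tumours, and eligibility does not require detectable plasma ctDNA.

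Among progressors who do have a detection, the order of events is nearly fixed by the schedule. Blood is drawn up to the visit at which imaging shows progression and then stops. The sequence of imaging first and ctDNA later is hardly observable, while any earlier positive sample, true or chance, counts as a gain of one or more visit intervals.

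What is at stake is how the figure is read. The Discussion argues that residual disease can be found before radiographic progression. A mean lead of several months would look like support for that, although an uninformative test produces one too.

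**Working it through.** The article states no lead-time figure, so there is nothing to reproduce. The check asks what the definition returns for a test that is pure noise.

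**Inputs from Sample size calculation.** 2-year PFS is 0.75 if ctDNA-negative and 0.50 if positive, with 30% positive at T3. Overall 2-year PFS = 0.3 × 0.50 + 0.7 × 0.75 = 0.675. Expected progressors among 57 enrolled = 57 × 0.325 = 18.5.

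**Assumptions.**
- Progression is exponential, with rate −ln(0.675)/24 = 0.01638 per month, and time is counted on the visit grid.
- Imaging detects progression at the next visit.
- Each sample is positive with probability q, independent of progression. The article gives no false-positive rate, so q runs from 0.02 to 0.30.
- ctDNA-detected recurrence is the first positive sample from T3 on.

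**Grids.** Table 1 suggests visits at 3, 6, 12, 18 and 24 months. The sampling text can also be read as 3, 9, 15 and 21 months. Both were run.

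**Worked case: q = 0.10, visits 3/6/12/18/24.**

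1. Share of progressors detected by imaging at each visit, from 1 − exp(−0.01638·t): w = 0.1475, 0.1404, 0.2610, 0.2366, 0.2144.
2. Share with any positive by the progression visit, Σ w_k[1 − 0.9^k] = 0.1475×0.1000 + 0.1404×0.1900 + 0.2610×0.2710 + 0.2366×0.3439 + 0.2144×0.4095 = 0.281. That is 0.281 × 18.5 ≈ 5 patients.
3. Expected lead over all progressors, Σ w_k Σ_{j≤k} 0.1×0.9^(j−1)(v_k − v_j). The inner sums are 0, 0.30, 1.44, 3.066 and 5.129, so the total is 0.1404×0.30 + 0.2610×1.44 + 0.2366×3.066 + 0.2144×5.129 = 2.24 months.
4. Mean lead among those with a detection = 2.24/0.281 = 8.0 months.
5. Share of progressors with a lead of exactly zero, Σ w_k × 0.1×0.9^(k−1) = 0.080. So 1 − 0.080/0.281 = 72% of computed leads are above zero, and none is below.

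**Full range, simulated with 400,000 patients per scenario.**

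| q | Progressors with a lead time (3/6/12/18/24) | Mean, months | Median, months | Mean on 3/9/15/21, months |
|---|---|---|---|---|
| 0.02 | 6% (about 1 of 18.5) | 7.6 | 6 | 6.1 |
| 0.05 | 15% (about 3) | 7.7 | 6 | 6.2 |
| 0.10 | 28% (about 5) | 8.0 | 6 | 6.5 |
| 0.20 | 49% (about 9) | 8.4 | 6 | 6.8 |
| 0.30 | 65% (about 12) | 8.8 | 9 | 7.1 |

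The median on 3/9/15/21 is 6 months throughout.

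**Visit windows.** With blood and scan dates each varying by ±2 weeks at T3 and ±4 weeks later, and same-visit blood allowed after the scan, 12-19% of values are negative. The lowest is −1.8 months, about two 4-week windows. The mean stays at 6.0 to 8.8 months. If blood drawn after the scan date is not counted, no value is negative and the means are about 7.8 to 10 months.

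**What drives it.** If samples after progression were observed (3/6/12/18/24 grid), 22-35% of the noise leads would be negative and the mean would fall to 1.5-4.8 months. If instead all progressors are kept and non-detections are set to zero, at q = 0.10 the median is 0 and the mean is 2.2 months (0.28 × 8.0), or about 1.5 on the other grid (0.24 × 6.5).

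**The case against.** The strongest reply is that the protocol does not ask lead time to carry the claim alone. Sensitivity, specificity, PPV, NPV and AUC are secondary outcomes, and kappa with contingency tables covers concordance at 3 months and at early relapse. A noise marker would tend to show an AUC near 0.5 and a kappa near 0 beside its lead time. This limits the harm but does not correct the lead-time figure, and the article does not say which visits enter specificity.

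The magnitude also rests on assumed positivity. Positive calls require a signal at the assay's LOD/LOQ, and trace results are not counted as definitively positive in the primary analysis, so a low rate is plausible. At 2% only about one progressor would carry a spurious lead. The 30% in the sample size section is the expected positivity of a prognostic marker, not a noise rate. Counting T3 positives also matters: if only later reappearance counts, at 5-10% per visit, the noise mean is 6.2 to 6.4 months. These points change the size, not the direction.

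Three stronger readings are tempting and not supported:
- That lead time can never be negative. The separate windows for blood and imaging allow small negatives.
- That the plan states that ctDNA-negative progressors are excluded. It names progressors as the population; the loss follows from needing two dates.
- That the study's main conclusions are compromised. The analysis is exploratory, and no test or sample size depends on it.

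**Conclusion.** The concern holds in limited form. Following the stated definition, sampling stop and shared visits gives an essentially one-sided lead time, restricted in practice to progressors with a detection. This is a consequence of rules the article fixes, not of detail left to an analysis plan, which could not recover blood that was never drawn.

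For an uninformative test the mean is about 6 to 9 months, among roughly 1 to 12 of about 18 progressors. That rests on assumed positivity of 2-30% per sample, exponential progression at 67.5% 2-year PFS, imaging at scheduled visits and counting the same-visit sample. The measure alone cannot show that ctDNA precedes imaging. Nor does the calculation show that ctDNA lacks a true lead; it shows only that this figure could not tell the difference. The primary PFS comparison and the numbered secondary outcomes are untouched.

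**What to change.** Reword the exploratory definition before recruitment starts:

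- Keep all patients with progression in the denominator, and report the share with ctDNA detected before, at, or not by the progression visit. Use the sample from that visit where available; it is already a scheduled blood visit.
- Give lead time among those detected only alongside that share.
- State whether persistence at T3 or only reappearance after clearance counts as ctDNA-detected recurrence.
- Report the share of non-progressors with a positive sample over the same visits. Matching matters because non-progressors have more samples: at 10% noise, 1 − 0.9^5 = 41% would have a positive over five visits, against 28% of progressors up to their progression visit.
- State that lead time is resolved only to the visit spacing and is one-sided by design.

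The comparator is the essential part. Setting non-detections to zero is not enough, since noise still leaves a mean of about 1.5 to 2.2 months at 10% positivity. Interval-censored modelling of both dates is not needed with about 18 progressors.

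The cost is one reworded paragraph, a little more analysis and a less favourable lead-time figure. No new scheduled visit is needed.

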### Sample size calculation

The sample size was calculated based on the primary endpoint of 2-year progression-free survival (PFS), comparing patients with detectable versus undetectable plasma HPV ctDNA at 3 months after completion of CCRT (T3). Institutional historical data indicate a 2-year PFS of approximately 75% in the ctDNA-negative group, while published studies suggest a rate of approximately 50% in the ctDNA-positive group (21). Based on prior studies of HPV-associated malignancies, we conservatively estimated that 30% of patients would be ctDNA-positive at the T3 assessment. Sample size was estimated using the log-rank test for comparing survival curves between two groups: 
$\text{n}={\left({\text{Z}}_{1}-\alpha {/}_{2}+{\text{Z}}_{1}-\beta \right)}^{2}/\left[{\left(\ln\text{HR}\right)}^{2}\times \text{p}\left(1-\text{P}\right)\right]$.

where 
$Z_{1-\alpha /2}=1.96$ for a two-sided α = 0.05, 
$Z_{1-\beta }=0.842$ for 80% power, and *p* = 0.30 represents the proportion of patients expected to be ctDNA-positive. The hazard ratio (HR) was derived from the assumed survival probabilities (
$S_{\text{ctDNA}+}=0.50$, 
$S_{\text{ctDNA}-}=0.75$), yielding an estimated HR of 2.41. Using these assumptions, a minimum of 48 evaluable patients is required to achieve 80% power to detect a difference in 2-year PFS at a two-sided significance level of 0.05. Allowing for an anticipated 15% attrition rate, the total target enrollment is 57 patients. This sample size is considered feasible for recruitment at a single high-volume tertiary cancer center over the planned 2-year enrollment period and is supported by effect sizes reported in prior studies of ctDNA as a prognostic biomarker in HPV-associated cancers (21, 22).

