### Feasibility and limitation

As a single-center study, external generalizability may be constrained by institutional practice patterns, patient demographics, and technical expertise in ctDNA analysis. Future multicenter studies across different regions, laboratories, and detection platforms will be required to externally validate the ddPCR thresholds, ctDNA clearance patterns, and predictive performance observed in this study. While the calculated sample size of 57 patients provides 80% power for the primary endpoint, subgroup analyses stratified by FIGO stage, histologic subtype, or baseline HPV type will have limited statistical power. Therefore, these analyses will be considered exploratory and hypothesis-generating, rather than confirmatory, and will mainly inform the design of future larger studies. The 24-month follow-up duration, while sufficient to capture most early recurrences, may inadequately characterize late relapses occurring beyond 2 years, particularly in patients achieving complete response. Long-term clinical follow-up will continue after completion of the planned 24-month study period, and updated analyses of long-term PFS, OS, and late recurrence patterns will be conducted in future reports. Pre-analytical variability represents another potential limitation; despite standardized protocols for blood collection, processing, and storage, factors such as hemolysis, delayed processing beyond 2 hours, or degradation during freeze-thaw cycles could influence ctDNA recovery and quantification (26). The absence of randomization precludes causal inference regarding ctDNA-guided therapeutic interventions, limiting the ability to demonstrate whether acting on ctDNA results improves outcomes compared to standard surveillance alone.

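### The sample-size formula returns 48 PFS events, but the plan reads the result as 48 patients; at 24 months power for HR 2.41 is about 36–49%, not 80%

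*Protocol article*

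**What the plan says.** In the Sample size calculation section of the protocol article, the planning rates are given as "Institutional historical data indicate a 2-year PFS of approximately 75% in the ctDNA-negative group" and "published studies suggest a rate of approximately 50% in the ctDNA-positive group", "yielding an estimated HR of 2.41". On prevalence, "we conservatively estimated that 30% of patients would be ctDNA-positive at the T3 assessment". The method is described thus: "Sample size was estimated using the log-rank test for comparing survival curves between two groups". The printed formula is n = (Z₁₋α/₂ + Z₁₋β)² / [(ln HR)² × p(1 − p)], with Z values 1.96 and 0.842.

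The result, with α = 0.05 (two-sided), is reported as "a minimum of 48 evaluable patients is required to achieve 80% power to detect a difference in 2-year PFS". It is then raised to 57 for 15% attrition.

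The Feasibility and limitation section repeats the claim: the "calculated sample size of 57 patients provides 80% power for the primary endpoint". It warns of limited power only for the subgroup analyses.

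**The concern.** The printed expression is the Schoenfeld formula for the total number of events in a two-group log-rank comparison. Its output equals a number of patients only if every patient progresses or dies within the analysis period. The same paragraph assumes that half of the ctDNA-positive patients and three quarters of the ctDNA-negative patients are progression-free at 2 years. The step from events to patients, which is division by the expected event probability, is absent.

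The power for the primary endpoint is the main quantitative claim of the design, and it appears twice. If it is wrong, readers are told that the primary comparison is adequately powered when, with 48 evaluable patients followed to 24 months, a non-significant log-rank test is more likely than not even if the assumed effect is true.

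**Working it through.** **Inputs, all from Sample size calculation:** two-sided α 0.05 (z = 1.96); target power 80% (z = 0.842); 2-year PFS 0.75 (ctDNA-negative) and 0.50 (ctDNA-positive); p = 0.30; attrition 15%. The 24-month follow-up is from Feasibility and limitation.

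**1. Reproducing the plan's figures**
- HR = ln 0.50 / ln 0.75 = 2.409, and ln HR = 0.8794.
- (1.96 + 0.842)² / (0.8794² × 0.30 × 0.70) = 48.3.
- 48 / 0.85 = 56.5, rounded up to 57.

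The plan's 2.41, 48 and 57 all reproduce, so the formula used is not in doubt. Rounding 48.3 down to 48 is trivial.

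**2. Expected events by 2 years**
- Event probability = 0.30 × 0.50 + 0.70 × 0.25 = 0.325.
- 48 patients: 48 × 0.325 = 15.6 events.
- 57 patients, no attrition: 57 × 0.325 = 18.5 events.

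**3. Power at HR 2.41, follow-up to 24 months**

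Power = Φ(√(d × 0.21) × 0.8794 − 1.96), where d is the number of events.
- d = 15.6: Φ(1.592 − 1.96) = 0.36.
- d = 18.5: Φ(1.734 − 1.96) = 0.41.

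A simulated log-rank test (exponential hazards, everyone censored at 24 months) is somewhat more favourable:

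| Evaluable | Events | Formula | Simulated |
|---|---|---|---|
| 48 | 15.6 | 36% | 43% |
| 57 | 18.5 | 41% | 49% |

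**4. Longer follow-up**
- Constant hazards, uniform 2-year accrual and at least 2 years for everyone: formula power 45% (48 patients) to 52% (57).
- Five years for every patient: PFS becomes 0.75^2.5 = 0.487 and 0.50^2.5 = 0.177. The event probability is 0.30 × 0.823 + 0.70 × 0.513 = 0.606, giving 29.1 and 34.5 events. Power is 58% and 66% by formula, and about 65% and 72% simulated.

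**5. Other methods that might have produced 48**
- Freedman with 3:7 allocation: about 38 events, or 117 patients.
- One-sided 0.05: 39 events, or 120 patients.
- Two proportions at 2 years: about 133 patients, with about 40% power at 48.

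None supports 48 patients.

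**6. HR at which 80% power is reached at 24 months**

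Negative-group 2-year PFS is held at 0.75, so the event count rises with the HR.
- 48 patients, HR 4.2: positive-group PFS = 0.75^4.2 = 0.299; event probability 0.385; 18.5 events; formula power 81% (79% at HR 4.1). Simulated power reaches 80% at HR about 3.7.
- 57 patients, HR 3.8: positive-group PFS 0.335; event probability 0.374; 21.3 events; formula power 81%. Simulated power reaches 80% at HR about 3.3 to 3.4.

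**The case against.** **Follow-up may exceed 24 months.** Recruitment spans 2 years, PFS is censored at the last adequate assessment before the analysis, imaging continues annually in years 3–5, and the article states no data cut-off. This stands in part: the 24-month figures are not the only possible ones, and a single range of 36–43% would describe only 48 patients all censored at 24 months. It does not rescue 80%, which is not reached even with 5 years for everyone. The calculation is also tied to 2-year PFS.

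**The true effect may be larger.** The Introduction cites hazard ratios above 4.0 and, for an earlier post-treatment sample, 2-year PFS of 82% versus 15%. This is fair, but the study is sized on 2.41, and the power claim has to be judged at that value.

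**Stronger readings that do not hold.** A reader might solve the formula for the HR while holding events at 15.6 or 18.5, obtain exp(2.802 / √(15.6 × 0.21)) = 4.7 or, for 57 patients, 4.1, and infer that the study is underpowered even for effects just above 4. Those event counts belong to HR 2.41. A larger HR brings more events: at HR 4.7, 48 patients would give about 19 events and formula power of 87%. A reader might also infer that the primary result will rest on a p-value alone. The Statistical analysis section already provides for hazard ratios with 95% CIs from Cox models, which lessens the risk of misreading a null result.

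**Condensed article.** This does not apply. The inputs, formula, result and power claim are all printed, and the error lies in what is stated.

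**Conclusion.** The point holds. The 48 is an event requirement labelled as a patient count, and the 80% power stated in Sample size calculation and in Feasibility and limitation is not delivered. On the plan's own assumptions about one third of the required events are expected (15.6 of 48.3). At HR 2.41 with 24-month follow-up, power is about 36–43% for 48 evaluable patients and 41–49% for 57.

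These figures assume constant hazards, 30% T3 positivity and 2-year PFS of 50% and 75%. Longer follow-up would raise them while leaving them below 80%. Events before the 3-month sample cannot be classified by T3 status, which would lower the usable count; the article gives no figure from which to quantify this.

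The finding does not show that the study is uninformative. It has about 80% power for HRs of roughly 3.3 to 4.2, depending on the number evaluable and the method.

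**What to change.** Keep n = 57 and correct the statements.

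- **Sample size calculation:** state that the formula returns 48 events; that about 16 (48 evaluable) to 18.5 (all 57) are expected by 2 years; and that power at HR 2.41 is about 36–49% under 24-month follow-up, with the assumptions given. Remove the 80% claim.
- **Detectable HR, if one is given:** let events rise with the HR, with negative-group 2-year PFS fixed at 75%. 80% power is reached at HR about 3.7 (simulated) to 4.2 (formula) with 48 evaluable patients, and about 3.3 to 3.8 with 57. Do not state 4.7 and 4.1.
- **Feasibility and limitation:** delete the 80% statement. Say that the primary comparison, like the subgroup analyses, has limited power, so a non-significant test does not show absence of prognostic value.
- **Statistical analysis:** no change, since hazard ratios with 95% CIs are already planned.

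The cost is rewording two paragraphs and accepting a less favourable power statement. Recruitment is planned from January 2027, so this can be done before the first patient. For information only, 80% power at HR 2.41 by 2 years would need about 48.3 / 0.325 = 149 evaluable patients, or 149 / 0.85 ≈ 176 enrolled; the correction does not depend on recruiting them.
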